# Implementation and evaluation of the VA DPP clinical demonstration: protocol for a multi-site non-randomized hybrid effectiveness-implementation type III trial

**DOI:** 10.1186/s13012-015-0250-0

**Published:** 2015-05-12

**Keywords:** Diabetes prevention, Implementation, Veterans, Pragmatic study design

## Abstract

**Background:**

The Diabetes Prevention Program (DPP) study showed that lifestyle intervention resulted in a 58% reduction in incidence of type 2 diabetes among individuals with prediabetes. Additional large randomized controlled trials have confirmed these results, and long-term follow-up has shown sustained benefit 10–20 years after the interventions ended. Diabetes is a common and costly disease, especially among Veterans, and despite strong evidence supporting the feasibility of type 2 diabetes prevention, the DPP has not been widely implemented. The first aim of this study will evaluate implementation of the Veterans Affairs (VA) DPP in three VA medical centers. The second aim will assess weight and hemoglobin A1c (A1c) outcomes, and the third aim will determine the cost-effectiveness and budget impact of implementation of the VA DPP from a health system perspective.

**Methods/Design:**

This partnered multi-site non-randomized systematic assignment study will use a highly pragmatic hybrid effectiveness-implementation type III mixed methods study design. The implementation and administration of the VA DPP will be funded by clinical operations while the evaluation of the VA DPP will be funded by research grants. Seven hundred twenty eligible Veterans will be systematically assigned to the VA DPP clinical demonstration or the usual care VA MOVE!® weight management program. A multi-phase formative evaluation of the VA DPP implementation will be conducted. A theoretical program change model will be used to guide the implementation process and assess applicability and feasibility of the DPP for VA. The Consolidated Framework for Implementation Research (CFIR) will be used to guide qualitative data collection, analysis, and interpretation of barriers and facilitators to implementation. The RE-AIM framework will be used to assess Reach, Effectiveness, Adoption, Implementation, and Maintenance of the VA DPP. Twelve-month weight and A1c change will be evaluated for the VA DPP compared to the VA MOVE! program. Mediation analyses will be conducted to identify whether program design differences impact outcomes.

**Discussion:**

Findings from this pragmatic evaluation will be highly applicable to practitioners who are tasked with implementing the DPP in clinical settings. In addition, findings will determine the effectiveness and cost-effectiveness of the VA DPP in the Veteran population.

**Electronic supplementary material:**

The online version of this article (doi:10.1186/s13012-015-0250-0) contains supplementary material, which is available to authorized users.

## Background

### Preventing diabetes

The Diabetes Prevention Program (DPP) study showed that lifestyle intervention resulted in a 58% reduction in incidence of type 2 diabetes among individuals with prediabetes [1]. Additional large randomized controlled trials have confirmed these results [2-4], and long-term follow-up has shown sustained benefit 10–20 years after the interventions ended [3,5]. Table 1 lists published type 2 diabetes prevention clinical trials and their results. These trials provide a strong evidence base for large-scale dissemination and implementation of the DPP to prevent type 2 diabetes.

**Table 1 Tab1:** **Published diabetes prevention program trial descriptions and selected outcomes**

Study	Individual or group	*N*(lifestyle group)	Years of follow-up	Mean weight loss (lifestyle group)	Reduction in developing diabetes
The Diabetes Prevention Program study [1]	Individual	1,079	2.8^a^	5.6 kg	58%
Diabetes Prevention Program Outcomes study [5]	Individual	910	10	2.0 kg	34%
The Finnish Diabetes Prevention Program study [42]	Individual	265	2	3.5 kg	58%^b^
China Da Qing Diabetes Prevention study [3]	Individual	266^c^	20	3.7 kg	43%
Indian Diabetes Prevention Programme [4]	Advice to individual^d^	133^e^	3	No significant change in body weight^f^	28.5%
DEPLOY YMCA [6]	Group	29	1	5.7 kg (6%)	NA
Group Lifestyle Balance [7]	Group	52^g^	1	5.5 kg (5.5%)	NA

^a^Follow-up ranged from 1.8–4.6 years.

^b^There was a 43% reduction in relative risk at a median of 7 years of follow-up; after a median of 4 years of active intervention period, participants who were still free of diabetes were further followed up for a median of 3 years [43].

^c^Number of participants, combined, across three lifestyle interventions: diet, exercise, and diet plus exercise.

^d^Participants received advice on healthy diet and regular physical activity.

^e^One hundred and thirty-three individuals were randomized to this intervention but 120 were available for follow-up at 2.5 years.

^f^Participants were younger (mean age 45.9 ± 5.7 years) and had lower BMI (25.8 ± 3.5 kg/m^2^) than previous studies.

^g^Number of participants that completed the 12-month assessment in a single group pre-post comparison study.

One significant barrier to implementing the DPP is the high cost of the individualized program. However, recent studies have shown that the program can be delivered at a lower cost in group sessions with comparable effectiveness [6,7]. For example, the Group Lifestyle Balance (GLB) program, a group-based adaptation of the DPP curriculum developed by the Diabetes Prevention Support Center (DPSC) of the University of Pittsburgh, resulted in clinically significant weight loss 12 months after baseline among program participants that completed the 12-month assessment [7,8]. GLB retains many of the components of the DPP, including standardized goals for weight loss, diet, and exercise and incremental introduction of self-regulation skills with a goal of self-regulation skill mastery.

Despite strong evidence supporting the feasibility of type 2 diabetes prevention, Veterans continue to be at high risk for developing type 2 diabetes. Primarily because of the older age of the population, the prevalence of type 2 diabetes is higher among Veterans who obtain care in the Veterans Affairs (VA) healthcare system than that in the general population, affecting approximately one in four Veterans [9]. In 2011, the Centers for Disease Control and Prevention (CDC) launched a national initiative to increase access to evidence-based DPP interventions for individuals with prediabetes [10], which contributed to the impetus for the current Veterans Affairs Diabetes Prevention Program (VA DPP) clinical demonstration.

### Preventing diabetes among Veterans

The VA National Center for Health Promotion and Disease Prevention (NCP) is the VA’s national program office responsible for many national disease prevention efforts. In 2006, NCP led the unprecedented implementation of VA MOVE!®, a national weight loss program within the VA [11]. VA MOVE! is an evidence-based, multi-disciplinary, comprehensive weight management program [11-14]. The core program includes eight to ten face-to-face small group sessions, led by a multi-disciplinary team of nutritionists, health psychologists, and physical therapists. While many elements of VA MOVE! are comparable to the VA DPP, Table 2 lists program design differences between the VA DPP and VA MOVE!. Additional file 1 provides further details. Within VA, over 95% of Veterans are screened for obesity, provided with obesity counseling, and offered VA MOVE! or another weight management program, as clinically appropriate [15,16]. Veterans are candidates for VA MOVE! if their body mass index (BMI) is greater than 30 kg/m2 or greater than 25 kg/m2 with one obesity-related condition. However, Veterans are not routinely screened for prediabetes, and with only a few exceptions, lifestyle modification programs that specifically target individuals with prediabetes are not available in the VA.

The VA DPP has been deemed a clinical quality improvement (QI) initiative. The implementation and administration of the VA DPP will be funded by clinical operations while the evaluation of the VA DPP will be funded by research grants. Because of the extremely short timeline, the research coordinating center submitted two separate research proposals, which are detailed in this protocol. Each research proposal was reviewed by a national peer review panel. The first proposal was submitted as part of the Quality Enhancement Research Initiative (QUERI) Rapid Response Project (RRP) program, which funds 1-year studies. This grant will enable the research coordinating center to collect baseline data as the VA DPP begins. The research coordinating center then submitted a QUERI Service Directed Project (SDP), which funds 2-year studies. This grant will enable the research coordinating center to collect and analyze follow-up data. Table 3 details the different funding sources and institutional review board (IRB) approvals for evaluation activities.

**Table 3 Tab3:** **VA DPP funding sources and IRB approvals**

Aims	Data type	Funding	IRB approvals
Quantitative data			
2	Weight and A1c lab results: baseline and follow-up	NCP QI^a^	Data collection approved as QI
		SDP^b^	Data access and analysis approved by five IRBs^c^
2, 3	Baseline patient surveys	RRP^d^	Approved by five IRBs
2, 3	Follow-up patient surveys	SDP	Approved by five IRBs
3	EQ5D survey	RRP	Approved by five IRBs
		SDP	
2, 3	Administrative utilization data linked to patient survey data	SDP	Approved by five IRBs for consented patients only
3	Staff time logs	NCP QI	Data collection approved as QI
			Data access and analysis approved by the research coordinating center’s IRB and the site conducting the cost analyses IRB
			• Included as information only in IRB applications for sites implementing the VA DPP
Qualitative data			
1	Early implementation staff interviews	NCP QI	Data collection approved as QI
		SDP	Data access and analysis approved by the research coordinating center’s IRB
			• Included as information only in IRB applications for sites implementing the VA DPP
1	Late implementation staff interviews, site visit field notes	SDP	Approved by the research coordinating center’s IRB
			• Included as information only in IRB applications for sites implementing the VA DPP
2	Patient interviews	SDP	Approved by the research coordinating center’s IRB
			• Included as information only in IRB applications for sites implementing the VA DPP
1	Fidelity assessments, meeting notes, document artifacts (e.g., emails)	NCP QI	Data collection approved as QI
		SDP	Data access and analysis approved by the research coordinating center’s IRB
			• Included as information only in IRB applications for sites implementing the VA DPP

^a^QI: quality initiative funded by the National Center for Health Promotion and Disease Prevention (NCP).

^b^SDP: Service Directed Project funded by the VA Quality Enhancement Research Initiative (QUERI) program; 2 year grant (12–549).

^c^IRB: Institutional Review Boards are located at the three sites implementing the VA DPP, the research coordinating center, and the site conducting the cost analyses.

^d^RRP: Rapid Response Project funded by the VA QUERI program; 1 year grant (12–440).

### VA DPP design

The VA DPP will run multiple cohorts per site, with the time intervals between the start of each cohort to be determined by site capacity. Each VA DPP cohort will include a series of 22 face-to-face GLB sessions using GLB materials, led by a coach with formal nutrition training and prior lifestyle coaching experience [17]. Table 4 details eligibility criteria for the VA DPP. Details about sample size and recruitment are provided under the “Aim 2” section below.

**Table 4 Tab4:** **VA DPP eligibility criteria**

Inclusion criteria	Exclusion criteria
Patients will be considered VA DPP eligible if all of the below are true:	Patients will be considered VA DPP ineligible if one or more of the following is true:
Patient has fasting glucose of 100–125 mg/dl OR A1c of 5.7%–6.4% for the past 6 months.	Patient already has type 2 diabetes. If patient was ever diagnosed with diabetes, they are not eligible, even if their A1c level is within the eligible range; they are then considered “diet controlled”.
Note: This is NOT the same as the VA’s criteria, which considers prediabetes as 5.7%–6.9%.	
	Patient does not have laboratory-confirmed elevations in either fasting glucose or A1c that indicates prediabetes.
Patient is VA MOVE! eligible (BMI ≥ 30 or BMI ≥ 25 with at least one cardiovascular disease risk factor).	
	Patient is taking metformin or other hypoglycemic agent.
	Patient is currently known to be pregnant.
Patient is competent to provide informed consent.	
	Patient has an eating disorder.
Patient understands English.	Patient has a medical contraindication to diet, exercise, or weight loss.
Patient has not used metformin for the past 3 months.	Patient is not competent to complete the informed consent process.
Travel time is <60 min from the VA medical center where patient receives their care.	Patient has attended all or part of VA MOVE! in the last year.
Patient has completed VA MOVE! introduction class.	Travel time is >60 min from the VA medical center where patient receives their care.

### VA DPP implementation strategy

The strategic framework for implementing the VA DPP will be an adaptation of Simpson et al.’s theoretical program change model for translating research into practice [18]. Figure 1 illustrates components of this framework.

**Figure 1 Fig1:**
[figure not shown]
VA DPP strategic framework for implementation.

Organizational readiness to implement a new program is demonstrated by stakeholders being internally motivated or externally pressured for change, which results in the allocation of resources necessary for implementation and administration of a new program [18]. The VA DPP site leaders must show commitment to diabetes prevention in order to successfully implement the VA DPP. NCP will provide all three VA DPP sites with program resources, including funding for staffing, training, and program materials.

### Phase one: adoption

In the VA DPP, exposure and training will take place after each VA DPP site’s Medical Center Director signs a formal memorandum of understanding (MOU) with NCP to demonstrate their commitment to the program. A clinical champion at each site will be responsible for shepherding the MOU through the approval process. This will require a series of presentations, conference calls, and meetings to inform all levels of local leadership about the VA DPP and to obtain a formal commitment from senior leaders to visibly support the project. The clinical champion will be responsible for hiring staff and coordinating with other site-specific resource teams that will be needed for the VA DPP, including the laboratory and the medical records teams. NCP leadership will help identify local supporters and provide visible authority (e.g., phone calls to leaders) at each site to further convey the importance of the project as it is being implemented.

#### Phase two: training

All team members will be trained at a 2-day GLB training program offered by the DPSC at the University of Pittsburgh. NCP will pay the costs for round-trip travel and registration for the training.

#### Phase three: implementation (exploratory use)

VA DPP cohorts will run in parallel to existing VA MOVE! groups. Implementation will rely on the existing VA MOVE! infrastructure for obesity screening, program referral, and medical clearance. Each site will develop a site-specific protocol that aligns the new processes for screening, identifying, informing, and assigning Veterans to the VA DPP within the existing VA MOVE! infrastructure. Protocols will also include processes for using the electronic medical record (EMR) system to track Veterans with prediabetes by VA DPP cohort. These institutional supports will be essential for monitoring and providing feedback to ensure successful implementation and administration of the VA DPP. The research coordinating center will facilitate weekly calls with VA DPP staff from each site to get status updates and provide collective problem-solving support during the implementation process.

#### Phase four: sustainability (routine use)

If the VA DPP is found feasible and effective, the challenge will be to sustain the program at each site and disseminate it more broadly within the VA. The goal of the evaluation study is to provide recommendations to NCP about how to scale-up the VA DPP, or its more successful components, at a national level.

### Research study aims

The research study design will follow the structure of an effectiveness-implementation hybrid type III trial [19]. Because of the strong evidence base for the DPP, the primary aim of this study will facilitate and evaluate implementation of the VA DPP at the three sites. However, because the DPP has not yet been evaluated in a Veteran population, the second aim will assess weight and hemoglobin A1c (A1c) outcomes for Veterans who enroll in the VA DPP. The third aim will determine the cost-effectiveness and budget impact of implementation of the VA DPP from a health system perspective. Specifically, the research study aims are:

#### Aim 1

The first aim is to evaluate an implementation strategy and identify barriers and facilitators to implementation of the VA DPP at three VA medical centers.

#### Aim 2

The second aim is to evaluate the effect of program implementation on participant outcomes, specifically weight and A1c values at 12 months, in the VA DPP compared to VA MOVE!, and assess patient engagement and adherence in the VA DPP.

#### Aim 3

The third aim is to conduct cost-effectiveness and budget impact analyses of implementing the VA DPP in the VA from the health system perspective.

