#### Data collection

##### Patient clinical outcomes

Weight will be measured with a medical-grade scale at each VA DPP and VA MOVE! session as well as at a 12-month program-specific session. Weight will also be routinely measured and documented in the EMR during other VA clinical visits. Baseline A1c and 12-month follow-up A1cs will be ordered by providers or the VA DPP coaches. A1c testing will occur via a laboratory blood draw or point of care (POC) testing. Attendance at all VA DPP and VA MOVE! sessions will be documented in the EMR by program session leaders.

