#### Data analysis

##### Patient surveys and clinical outcomes

Effects of the VA DPP and VA MOVE! on patient outcomes at 12 months will be assessed using clinical weights and A1c lab values. The distribution of all study variables and baseline differences in factors that may affect study outcomes between groups will be assessed. If significant differences are found, they will be included as covariates in the final analyses. At each assessment time, cross-sectional means and their associated 95% confidence intervals for continuous outcomes (e.g., weight) will be described. Comparison between the VA DPP and VA MOVE! in weight loss at 12 months will be completed with a linear mixed-effects model, using program arm as random intercepts to account for potential intra-program group correlation. The model will include the primary predictor of program arm (the VA DPP or VA MOVE!), indicators for the three study sites, baseline weight values, and age, sex, and race variables. Time-averaged effects of the VA DPP over VA MOVE! will be compared using weight loss at 12 months as the dependent variable. The model will allow the use of all available data, even if some Veterans are missing 12-month weights, and will give an unbiased estimate as long as missingness does not depend on the unobserved missing outcomes. Careful graphical analyses of longitudinal outcome data will be completed to ensure that an appropriate and meaningful longitudinal model is created. Additional file 7 describes the planned mediation analyses.

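### A1c is worded as a change in one place and as a 12-month value in another, and baseline A1c enters its analysis only if it passes a significance test

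*Protocol article*

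**What the plan says.** The Abstract (Methods/Design) says: "Twelve-month weight and A1c change will be evaluated for the VA DPP compared to the VA MOVE! program". Research study aims, Aim 2, instead names participant outcomes as "specifically weight and A1c values at 12 months, in the VA DPP compared to VA MOVE". Aim 3 (Analysis) returns to change: changes in A1c are an input to the lifetime cost-effectiveness model.

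Under Aim 2, Data analysis (Patient surveys and clinical outcomes), "patient outcomes at 12 months will be assessed using clinical weights and A1c lab values", which names the measurements without choosing between value and change. The only model written out is for weight: "Comparison between the VA DPP and VA MOVE! in weight loss at 12 months will be completed with a linear mixed-effects model". Besides arm, it contains "indicators for the three study sites, baseline weight values, and age, sex, and race variables". For other baseline variables the same paragraph gives a general rule: "baseline differences in factors that may affect study outcomes between groups will be assessed", and then "If significant differences are found, they will be included as covariates in the final analyses".

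Baseline A1c will be available in principle. Under Patient clinical outcomes, "Baseline A1c and 12-month follow-up A1cs will be ordered by providers or the VA DPP coaches". Assignment is not random: in each two-month cycle the first 20 eligible patients go to VA DPP and the next 20 to VA MOVE! (Aim 2, Study participants).

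**The concern.** For weight, the choice between change and 12-month value does not matter, because baseline weight is always in the model and the arm effect is then the same on either scale. Nothing gives A1c the same protection. As written, baseline A1c is adjusted for only when the arms happen to differ significantly on it.

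A non-significant difference is not evidence of balance, least of all when arms are filled by order of eligibility. Letting a test decide also means that the quantity estimated depends on the data. If baseline A1c stays out, the A1c result depends on which wording the analyst follows. A1c is one of the two outcomes named in Aim 2 and also feeds the economic evaluation.

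**Working it through.** The article gives no A1c effect size, SD, correlation or power, so there is no stated A1c figure to reproduce. The check has four parts.

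**1. Wording for the two outcomes**

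| Place | Weight | A1c |
|---|---|---|
| Abstract, Methods/Design | 12-month change | 12-month change |
| Aim 2 statement | value at 12 months | value at 12 months |
| Aim 2, Data analysis | weight loss at 12 months, baseline weight always included | lab values; scale and baseline covariate not settled |
| Aim 3, Analysis | not listed among the named inputs | change |

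**2. Effect of the choice of scale.** Let *d* be the baseline arm difference in the patients analysed.

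- Unadjusted: difference in change = difference in 12-month value − *d*. The two analyses are therefore exactly *d* apart. This is an identity and needs no assumption.
- With baseline A1c as a covariate: subtracting baseline from the outcome lowers the baseline coefficient by 1 and leaves the arm coefficient unchanged. The two analyses agree.
- Simulated illustration (288 per arm, correlation 0.6, no true effect): unadjusted value difference 0.2943 SD, unadjusted change difference −0.0311 SD, gap 0.3254 SD, equal to the baseline difference in that sample. Adjusted for baseline, both give 0.1141 SD.

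**3. How large *d* can be and still escape the screen.** Inputs from Aim 2, Study participants: 360 per arm, 20% dropout (360 × 0.8 = 288), intra-group correlation .014, 20 per cohort, so a design effect of 1 + 19 × 0.014 = 1.266. The limit is 1.96 × √(2 × DE / n) in SD units.

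- 360 per arm, DE 1: 1.96 × √(2/360) = 0.146 SD.
- 288 per arm, DE 1.266: 1.96 × √(2 × 1.266/288) = 0.184 SD.

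With an assumed A1c SD of 0.2 to 0.4 points (not in the article), that is about 0.03 (0.146 × 0.2) to 0.07 (0.184 × 0.4) A1c points. A larger imbalance would be significant, and the rule would bring baseline A1c in.

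These are ceilings. If the imbalance is pure chance, the mean |z| given |z| < 1.96 is about 0.72. A typical *d* is then 0.72 × √(2/360) = 0.054 SD to 0.72 × √(2 × 1.266/288) = 0.068 SD, a little over a third of the ceiling.

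**4. Precision.** With equal variances and correlation *r*, adjustment reduces variance by *r*² against the value analysis and by (1 − *r*)/2 against the change analysis. At an assumed *r* of 0.6 these are 36% and 20%; over *r* from 0.4 to 0.8 they are 16–64% and 30–10%.

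**The case against.** Several stronger readings are tempting, and the article does not support them.

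- **Two rival A1c endpoints.** A reader might infer this from the Abstract and Aim 2. But Aim 2 uses the same wording for weight, which is then analysed as weight loss, so it is probably shorthand. The Abstract and the economic section both point to change. What stands is that only the weight wording is settled later.
- **A faulty model.** A reader might say that the stated model wrongly omits baseline A1c. That model is for weight loss, and baseline weight is the right covariate there. An A1c model may sit in the full protocol or analysis plan, so its absence from an article is not a finding. What stands is the general covariate rule, which the article does state.
- **The A1c comparison carries baseline imbalance.** Baseline A1c plainly falls under the covariate rule, so a significant imbalance would be adjusted for. Only imbalance that escapes the screen remains.
- **The value and change analyses err in opposite directions.** Suppose both arms share one regression of 12-month on baseline A1c, with slope β = *r* × (12-month SD / baseline SD). The unadjusted value then carries β*d* and the change carries (β − 1)*d*. The signs are opposite only if β lies between 0 and 1. At *r* = 0.6 and an SD ratio of 1.67, β is about 1 and the change analysis is unbiased. If the arms differ in stable mean A1c, change may be the better estimator and baseline adjustment the biased one.
- **The gap is 1.7 to 2.7 standard errors of the adjusted estimate.** That range follows from 0.146 / (√(1 − *r*²) × √((2/288) × 1.21)) for *r* of 0.4 to 0.8. It puts *d* at the edge of significance, uses 360 unclustered patients per arm for *d* but 288 clustered ones for the error (1.21 = 1 + 15 × .014), and assumes the correlation and equal variances. It is a worst case.
- **Eligibility confines A1c to 0.7 points.** Table 4 also admits patients on fasting glucose of 100–125 mg/dl, so baseline A1c need not lie between 5.7% and 6.4%.

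**Conclusion.** The point holds in limited form. The A1c wording is inconsistent and is resolved for weight only. The stated rule makes adjustment for baseline A1c depend on a significance test, which is poor practice in a systematically assigned, non-randomised comparison.

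The firm part is the identity: without adjustment, the two A1c analyses differ by exactly the baseline arm difference. The screen caps that at about 0.15 to 0.18 SD, depending on the numbers and clustering assumed. Any figure in A1c points, any signed bias and any precision gain rests on an SD, a correlation or variances that the article does not give.

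Implementation is the primary aim and the power calculation concerns weight, so this is a worthwhile low-cost improvement to a secondary-aim outcome. It does not threaten the study's main conclusions and does not touch the weight model.

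**What to change.** Use one A1c definition in the Abstract, the Aim 2 statement and the Aim 2 data analysis section: the arm difference in 12-month A1c, adjusted for baseline A1c. State that the A1c model contains arm, site, age, sex, race and baseline A1c, with baseline A1c included whatever its baseline p-value, mirroring the weight model. The adjusted arm difference reads the same as change or as value, so the wording conflict then has no consequence.

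The cost is about one sentence of analysis text and matching wording elsewhere. Baseline A1c is already due to be collected. The small downside is that Veterans who qualified on fasting glucose may lack a baseline A1c, so an approach to missing baselines should be stated. Under Trial status, cleaning or analysis of 12-month outcomes had not begun at submission, so on that status the definition could be fixed before results are seen.
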